### Main Outcomes

The primary end point for efficacy is the change in the VAS score for neck pain from baseline (day 1: before application) to the end of the study drug application (day 15).

The secondary efficacy end points are as follows:

Change in the VAS score for neck pain from baseline (day 1: before application) to the end of the clinical study (day 29).Changes in grip strength from baseline to the end of the drug application (days 1-15) and the end of the study (days 1-29).Changes in VAS scores for subjective symptoms (feeling of strangulation, numbness, swelling, and warmth) from baseline to the end of the drug application (days 1-15) and the end of the study (days 1-29).Whether the VAS score for neck pain showed a ≥30% improvement from baseline to the end of the drug application (days 1-15) and the end of the study (days 1-29).Change in arm abduction [27] from baseline to the end of drug administration (days 1-15) and the end of the study (days 1-29).Change in shoulder joint range of motion (abduction and flexion) from baseline to the end of drug application (days 1-15) and the end of the study (days 1-29).

The secondary end point for safety is the presence or absence of adverse events such as skin disorders and serious diseases. The relationships among the interventions, outcomes, other assessments, and visits associated with the participants in this study are shown in Table 1.

### Statistical Analysis

The primary objective of this clinical study was to evaluate the efficacy of the CO_2_ paste versus the placebo in terms of the change in VAS scores for neck pain (the primary end point). For the comparison of the primary end point, the Wilcoxon test will be performed for the null hypothesis, “There is no difference in the change in VAS values for neck pain at day 15 between the placebo group and the CO_2_ paste group.” The significance level will be set at 5.0% (1-sided). Each evaluation item will be summarized. Secondary efficacy end points will be analyzed to provide additional insights into the primary analysis. No adjustment for multiplicity will be made in the analyses of the secondary efficacy end points. The significance level for hypothesis testing is 5% (2-sided) with 2-sided 95% CIs. The incidence and rate of disease will also be evaluated. The safety end point is the frequency of the occurrence of adverse reactions. Tables will be prepared for the end points, and exact 2-sided 95% CIs of the binomial distribution will be calculated for each group to estimate the proportions.

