### Data Collection

The data collection schedules are presented in Table 1. The primary investigator or subinvestigator will enter the case report form (CRF) data for each participant into the electronic data capture (EDC) system. The principal investigator will confirm that the entered CRF data are complete and correct, electronically sign the CRF on the EDC system, and print out the signed CRF for filing. The CRF printout will be retained. If any queries about the CRF data are entered by the staff at the data center, the primary investigator or subinvestigator will be required to promptly respond to them.

**Table 1 table1:** Data collection schedule.

	Registration (within 4 weeks before allocation)	Preobservation (7±3 days before allocation)	Allocation day 1 (preapplication)	Allocation day 1 (postapplication)	Postallocation day 15+1 (finish application)	Postallocation day 29+3	Exclusion	Within 7 days after exclusion
Assessment of eligibility criteria	✓							
Obtain consent	✓							
Registration	✓							
Patient characteristics^a^	✓							
Allocation and start of the application			✓					
VAS^b^ of neck pain		✓	✓	✓	✓	✓		
VAS values of subjective symptoms^c^			✓	✓	✓	✓		
Strength of grip arm abduction test^d^ Shoulder joint range of motion (abduction or flexion)			✓		✓	✓		
Adverse events				✓	✓	✓	✓	✓
Vital sign^e^	✓		✓	✓	✓		✓	✓
Oxygen saturation (SpO_2_)	✓		✓				✓	✓
Confirmation of days of application					✓		✓	

^a^Sex, date of birth, age, medical history, comorbidity, primary disease, TNM classification, the number of days after surgery, the range of neck dissection, preservation of sternocleidomastoid muscle, accessory nerve, and internal jugular vein, and the details of adjuvant therapy.

^b^VAS: visual analog scale.

^c^Strangulation, numbness, swelling, and warmth.

^d^Arm abduction test: up to 180˚ without pain or effort (5 points), up to 180˚ but with pain or effort (4 points), up to more than 150˚ but less than 180˚ (3 points), up to more than 90˚ but not less than 150˚ (2 points), up to approximately 90˚ (1 point), and up to less than 90˚ (0 point) [27].

^e^Body temperature, blood pressure, and pulse rate.

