### Sample Size Calculation

Most patients are expected to have a baseline VAS score of 2-3 cm. For the primary end point (the amount of change in VAS values for neck pain), we estimated that the mean difference in change between the CO_2_ paste application and placebo groups would be 2 (SD 1.5) cm. A Wilcoxon test (a nonparametric test) will be performed considering the possibility that participants with a baseline score of less than 2 cm might be enrolled. The number of cases based on the Wilcoxon test can be calculated by multiplying the number of cases based on the *t* test [28]. Although the constant for multiplication is 1.045 in the case of a normal distribution, since the participants in this study were not assumed to be normally distributed, the number of cases was calculated by multiplying by 1.2. When conducting a *t* test with a 1-sided significance level of 5.0% and a power of 80%, a total of 7 participants were required per group. When the number of cases was multiplied by 1.2, the total number of cases was 8.4. Therefore, considering drop out cases, 20 cases would be sufficient to maintain power.

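### The primary Wilcoxon test ranks raw VAS change without adjusting for baseline: it is valid and has enough power at the planned effect, but gives up some precision that data already collected could recover

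*Protocol article*

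**What the plan says.** All places are in the protocol article.

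- **End point (Main Outcomes).** "The primary end point for efficacy is the change in the VAS score for neck pain from baseline (day 1: before application") to day 15. This is a raw difference.
- **Test (Statistical Analysis).** "For the comparison of the primary end point, the Wilcoxon test will be performed for the null hypothesis" of no group difference in that change, at a one-sided 5% level. No covariate or stratified version of the test is named.
- **Reason for the test (Sample Size Calculation).** The Wilcoxon test is chosen "considering the possibility that participants with a baseline score of less than 2 cm might be enrolled".
- **Planning values (Sample Size Calculation).** The "mean difference in change between the CO_2_ paste application and placebo groups would be 2 (SD 1.5) cm". The t-test size is 7 per group. It is multiplied by 1.2, and 20 patients in total are planned.
- **Baseline range.** The scale runs from 0 to 10 (Objectives), entry requires a score of at least 1 (inclusion criteria), and most patients are expected at 2 to 3 cm (Sample Size Calculation).
- **Pre-treatment readings (Table 1).** Neck-pain VAS is taken at "Preobservation (7±3 days before allocation") and again on day 1 before the first application. The stated primary comparison uses only the second, by subtraction.

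**The concern.** Improvement cannot exceed the starting score. A patient who goes from 1 to 0 has complete relief, yet ranks below a patient who goes from 3 to 1.5. The plan recognises that low baselines are awkward and answers with a rank test. Ranks protect against non-normal changes, but they leave the link between change and baseline as it was.

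A change score also corrects for baseline with a fixed slope of 1. If the true slope of day-15 VAS on baseline is below 1, this over-corrects: the arm that happens to start higher appears to improve more. With 10 patients per arm, chance differences in baseline are to be expected. What is at stake is the precision of the primary comparison in a very small trial.

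**Working it through.** **1. The plan's own figure.** Inputs from Sample Size Calculation: difference 2 cm, SD 1.5 cm (read as the SD of change), one-sided 5%, power 80%.

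n per group = 2 × [1.5 × (1.645 + 0.842) / 2]² = 6.96, so 7. Then 7 × 1.2 = 8.4, so 9 per group or 18 in all, and 18 / 0.9 = 20, which leaves room for 10% dropout. The stated size reproduces.

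**2. The cap.** A 2 cm improvement is 67% of a 3 cm baseline, 80% of 2.5 cm and 100% of 2 cm. It is impossible from 1 cm.

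**3. Validity and power of the stated test.** In simulations with 10 per arm and SD of change 1.5 cm (4,000 trials per setting), the Wilcoxon test on change had type I error of 4.2 to 5.4% and about 86% power at 2 cm.

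**4. Chance imbalance.** The 95% range of the baseline difference is ±1.96 × s × √(2/10), where s is the baseline SD (not given, so assumed). For s = 0.5, 1.0 and 1.5 cm this is ±0.44, ±0.88 and ±1.31 cm. With slope b, an imbalance D shifts the difference in change by (b − 1) × D. At b = 0.5 and D = 0.5 cm the shift is 0.25 cm, in favour of the arm that started higher. Half of the imbalance therefore remains, with its sign reversed.

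**5. Variance saved by ANCOVA.** Write Var(change) = (1 − b)² s² + e² = 1.5² = 2.25, where e² is the variance left after adjustment. The ratio of ANCOVA to change-score variance is 1 − (1 − b)² s² / 2.25, before the small cost of estimating the slope. The slope b = 0.5 is assumed.

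**6. Power at a true difference of 1.5 cm** (10 per arm, one-sided 5%, 3,000 trials per setting, no floor):

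| Baseline SD (cm) | Variance ratio | Wilcoxon on change | ANCOVA | Rank ANCOVA |
|---|---|---|---|---|
| 0.5 | 0.97 | 65% | 69% | 67% |
| 0.7 | 0.95 | 65% | 69% | 67% |
| 1.0 | 0.89 | 64% | 70% | 68% |
| 1.5 | 0.75 | 66% | 78% | 74% |

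Repeat runs put the ANCOVA gain over Wilcoxon at about 3 to 5 points for SD 0.5 to 0.7, 6 to 8 for SD 1.0 and 12 to 13 for SD 1.5. An unadjusted t test on change already reaches about 69%. At SD 0.5 to 0.7, therefore, the gain comes from leaving ranks, not from adjusting.

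**7. With the floor at 0.** This model assumed a skewed baseline (median 2.5 cm, at least 1), placebo patients keeping 85% of baseline pain, active patients keeping 30 or 50 percentage points less, and 4,000 trials per setting:

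| Noise SD (cm) | Extra relief | Wilcoxon | ANCOVA | Rank ANCOVA |
|---|---|---|---|---|
| 0.7 | 30 points | 64% | 75% | 65% |
| 1.0 | 30 points | 45% | 51% | 44% |
| 1.0 | 50 points | 76% | 85% | 80% |
| 1.5 | 30 points | 28% | 30% | 28% |

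ANCOVA kept type I error at about 5% here (4.7 to 5.3%). Rank ANCOVA gained little or nothing in several settings.

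**The case against.** The strongest reply is that nothing here is wrong. The test is valid, conventional and prespecified, the trial calls itself exploratory, and at the planned 2 cm the test exceeds its 80% target. All of that stands, and it limits the point to precision.

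Four stronger readings are tempting, and the document does not support them.

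- **That adjustment saves 25 to 35% of the variance.** The usual formula (1 + ρ)/2 gives this at correlations of 0.5 and 0.3, but it assumes equal variances at both visits. With SD of change 1.5 cm it implies a baseline SD of 1.5 / √(2(1 − ρ)), which is 1.5 and 1.27 cm. If baselines are roughly normal around 2.5 cm, having most of them between 2 and 3 cm requires an SD of about 0.74 or less. An SD of 1.5 would put only 26% in that range and 16% below the entry limit. A long upper tail could raise the SD, but none is described.
- **That baseline imbalance goes uncorrected.** It is corrected, with a slope fixed at 1. Only the excess correction remains.
- **That the preobservation VAS is never used.** The article condenses a fuller protocol, and the analysis plan is not shown. It can be said only that the stated primary test does not use that reading.
- **That patients with low baselines are ignored.** The secondary end point of at least 30% improvement addresses relative relief.

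Randomization is also stratified by a category that is not named. If that category were baseline VAS, imbalance would be smaller, although the stated test would still not use it.

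Finally, ANCOVA leans on a linear model, and the plan expects non-normal data. A permutation p-value meets most of this concern, and keeping the Wilcoxon result beside it meets the rest.

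**Conclusion.** The point holds as an inexpensive improvement, not as an error. The stated primary test leaves change dependent on baseline, and its stated reason does not cure that. Its type I error is near 5%, and its power is about 86% at the planned effect with 20 completers.

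The size of the loss cannot be fixed from the document, because neither the baseline SD nor the slope is given. Under the assumptions in the working (slope 0.5, true difference 1.5 cm), it is small if baselines cluster as tightly as the plan expects, and material only if they spread to an SD of 1 cm or more. A true effect below 2 cm, where power is no longer comfortable, is plausible because 2 cm already means complete relief from a 2 cm baseline.

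**What to change.** Before unblinding, make the primary comparison an ANCOVA of day-15 neck-pain VAS with treatment and pre-treatment VAS as terms. Take the p-value from a permutation test, because only 20 patients are planned. The covariate can be the day-1 pre-application value or its mean with the preobservation value; state which. With the day-1 value as covariate, modelling day-15 VAS or change gives the same treatment effect, so the primary end point need not be redefined.

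Keep the unadjusted Wilcoxon test on change as a sensitivity analysis. Do not make rank ANCOVA the preferred method, because it gains little or nothing near the floor.

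The cost is one added sentence in the statistical section and slightly more analysis work. No new data or patients are needed.

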### Sample Size Calculation

Most patients are expected to have a baseline VAS score of 2-3 cm. For the primary end point (the amount of change in VAS values for neck pain), we estimated that the mean difference in change between the CO_2_ paste application and placebo groups would be 2 (SD 1.5) cm. A Wilcoxon test (a nonparametric test) will be performed considering the possibility that participants with a baseline score of less than 2 cm might be enrolled. The number of cases based on the Wilcoxon test can be calculated by multiplying the number of cases based on the *t* test [28]. Although the constant for multiplication is 1.045 in the case of a normal distribution, since the participants in this study were not assumed to be normally distributed, the number of cases was calculated by multiplying by 1.2. When conducting a *t* test with a 1-sided significance level of 5.0% and a power of 80%, a total of 7 participants were required per group. When the number of cases was multiplied by 1.2, the total number of cases was 8.4. Therefore, considering drop out cases, 20 cases would be sufficient to maintain power.

### Monitoring for Human Rights, Safety, and Adequacy

Monitoring will be conducted periodically to check whether the human rights and safety of the participants are protected and to confirm that the regulatory requirements of the Clinical Trials Act are followed. To ensure an appropriate assessment, the principal investigator is responsible for dealing with personal data and items specified in the written procedure. Any requirements made by the ethics committee will be immediately announced to the participants by the study investigators.

### Other Considerations

This study will be conducted without patient or public involvement. Neither the patients nor the public will be involved in the development of the research question, study design, or implementation of the trial. Patients will not be invited to develop patient-relevant outcomes, interpret the results, or participate in the writing or editing of the final manuscript. Since the interventions in this study are routine clinical procedures, the burden of the interventions will be assessed by the patients themselves.

Any protocol changes that affect the study conduct or participant risk-benefit profile will require approval from the relevant institutional review board, including changes in the objectives, design, sample size, participant characteristics, staff changes, or significant administrative features. Minor protocol corrections or clarifications that do not affect the study conduct or the participant risk-benefit profile will be viewed as administrative changes and documented internally. The study investigators will have full access to and ownership of all the data. Anonymized data will be made available to other interested investigators for additional analyses on reasonable request, following reports of primary outcomes and with an appropriate data use agreement. The findings of this study will be disseminated through scientific and professional conferences and a peer-reviewed journal.

### Ethical Considerations

The study is being conducted in compliance with the principles of the Declaration of Helsinki (1996), the principles of good clinical practice, and all applicable regulatory requirements. This study has been approved by the Clinical Research Review Board of Kobe University (CRB5180009), and the trial has been registered with the Japan Registry of Clinical Trials (jRCT) (jRCTs051210028). All participants will be required to provide written informed consent before any study procedures are conducted. The participants will have the opportunity to review the consent form and confirm that they have fully understood the details of the study procedures. Secondary use of the data will occur only if the patients provide written informed consent for additional use of their data. Secondary use of the data will adhere to appropriate ethical review and approvals, as per institutional guidelines. No funding was received for this study, including institutional or departmental support. The study is not commissioned, externally peer reviewed.

## Results

The subject recruitment began on May 24, 2021. The entry period for participants is up to March 31, 2024, three years after the jRCT registration. Data analyses of all enrolled participants will be conducted in 2024. This manuscript is based on the current version of the protocol (version 3.0), last updated on December 23, 2022.

The data sets generated in this study will be available on the jRCT website. The final report is expected to be published in a peer-reviewed journal in 2025. The findings will be disseminated through scientific and professional conferences and peer-reviewed journal publications in 2025.

## Discussion

### Expected Findings and Implications

This report describes the protocol for a study evaluating the application of CO_2_ paste to patients who undergo neck dissection and experience postoperative complaints. A neck dissection is a surgical procedure performed to remove cervical lymph nodes. During surgery, the blood vessels are ligated to prevent bleeding. In addition, the internal jugular vein, which drains blood from important organs such as the brain, face, and neck, is removed depending on the type of neck dissection. These blood flow interruptions lead to wound ischemia and various postoperative symptoms or dysfunctions.

Pain, the main side effect of neck dissection, often aggravates patient QOL [1,7]. As its pathogenesis remains uncertain, a treatment strategy for postoperative pain has not yet been established. Analgesics such as nonsteroidal anti-inflammatory drugs and acetaminophen are commonly administered to relieve this pain. Nonsteroidal anti-inflammatory drugs show remarkable efficacy as painkillers; however, they are also associated with serious adverse reactions in the gastric mucosa and cardiovascular, hepatic, renal, and hematological systems [29]. Although almost all patients receive acetaminophen [30], those undergoing neck dissection continue to experience pain. Considering the limitations of drug therapy, effective treatment of every patient with postoperative pain is essential.

In a phase 1 clinical study, we reported that CO_2_ paste application increases blood flow to the skin and muscles without any side effects [26]. Since transcutaneous CO_2_ application induces angiogenesis by inducing an artificial Bohr effect, we hypothesize that this simple and adaptable treatment can alleviate side effects and improve the QOL of patients undergoing neck dissection.

This study will be the first to apply CO_2_ paste to postoperative skin. Since it is composed of food ingredients, the CO_2_ paste is considered to have few life-threatening side effects. However, there is no evidence on whether its application may induce dermatitis. Therefore, the occurrence of dermopathies such as erythema and exanthema should be carefully monitored during the trial. To address potential safety concerns, the CO_2_ paste will be applied to the postoperative neck for only 10 minutes a day.

Through this study, we aim to determine the curative effect of CO_2_ paste application on postoperative neck pain in patients undergoing neck dissection. Since the efficacy of CO_2_ paste for neck pain has never been reported, this will be the first well-designed clinical evaluation study on this topic. Our primary hypothesis is that CO_2_ paste application can reduce pain in patients undergoing neck dissection. We also expect that the application of this paste will reduce subjective symptoms, including feelings of strangulation, numbness, swelling, and warmth, and will improve grip strength, arm abduction, and shoulder joint range of motion (abduction and flexion).

### Study Strengths and Limitations

We previously conducted a clinical trial on a small number of healthy individuals. To explore the adequacy and applicability of CO_2_ paste application, this will be the first protocol to be performed as a phase 2, double-blinded, randomized controlled trial, evaluating the efficacy of CO_2_ paste in a small number of patients with neck pain after neck dissection. Nonetheless, this clinical trial has some limitations that should be acknowledged. First, the number of evaluated patients is relatively small to conclusively determine the efficacy of the CO_2_ paste. Second, since some patients underwent neck dissection as part of larger resections, a small amount of heterogeneity is expected. Finally, this study is limited by its short duration (28 days).

### Conclusions

Considering the general condition of the patients and the side effects of drug therapy, postoperative pain after neck dissection is difficult to manage. Therefore, establishing a widely applicable treatment with fewer adverse effects is essential. The results of this study will provide valuable evidence for the future application of CO_2_ paste to patients complaining of pain after neck dissection.

## Abbreviations

CO_2_: carbon dioxide
CRF: case report form
EDC: electronic data capture
jRCT: Japan Registry of Clinical Trials
QOL: quality of life
REDCap: Research Electronic Data Capture
VAS: visual analog scale
